#### Qualitative Analysis

In the qualitative analysis, we will use interpretive description as a methodology [53-55]. Interpretive description aims to generate a practical understanding of the importance of applied disciplines within their context [53]. The interpretive description analysis will be performed in parallel with the data collection. All data from the transcribed interviews and field notes from the participant observation will be included in the analysis. Interpretive description analysis is an inductive, open, and exploratory approach that includes a constant comparative analysis. Hence, it builds from specific data toward a broader generalization. This analysis will lead to the identification of final themes describing patients’ acceptability of digital communication and how patients and diabetes health care personnel use the technology [53]. The NVivo software is used for data management, coding, and analysis [56]. The initial coding phase will be broad-based inductive coding into categories, followed by fine-tuned coding and interpretation of the data.

### User Involvement

In this study, health care personnel will participate alongside patients and stakeholders to adapt the DiabetesFlex to a Norwegian context, resulting in a set of PROM items that may be highly relevant to the patients. On the basis of their answers, health care personnel can triage their patients to offer suitable treatment when needed through a traffic light model. User involvement regarding the project’s development has been described elsewhere [25]. In addition, a reference group for the project will be established, containing individuals with type 1 diabetes, diabetes specialist nurses, endocrinologists, management, and researchers.

### Ethical Considerations

The Data Protection Office approved the study at Akershus University Hospital (2022_125). Patients at the outpatient clinic will be screened for eligibility for the study by health professionals, and all patients meeting the inclusion criteria will be offered the digital PROM. Therefore, a randomized controlled trial is impossible, and the proposed study has no control group. However, those declining to engage in digital tools will act as a comparative group in the analysis. All participants will provide their written informed consent before the study starts. All data will be securely stored in Services for Sensitive Data. Data shared in the MyDignio app will be encrypted and stored according to legislation on the privacy and secure storage of sensitive health information. The Data Protection Office performed a comprehensive risk assessment analysis of the technology upon initiation, and the research team completed a risk assessment analysis of the risks related to the conduct of the research before the start of the study. SIKT—the Norwegian Agency for Shared Services in Education and Research—will be notified per the Norwegian protocol to assess project data protection and information security.

To ensure data safety, patients must use their national ID to identify themselves, either through BankID or MinID, both to provide their digital consent and self-report on the digital questionnaires of the research evaluation and to log in when using MyDignio.

## Results

The study received funding in March and October 2022 from Oslo Metropolitan University–OsloMet internal funding. The digital solution was implemented in clinical care at the department in November 2021, and the first participant was enrolled in the research project with a completed T0 on October 27, 2022. As of September 6, 2023, a total of 220 patients have been enrolled in the project, of which 84.5% (n=186) are digital users and 15.5% (n=34) are nonusers in the comparative group. The data collection is projected to end during 2024.

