**Results:**

The digital solution was implemented for routine clinical care in the department in November 2021, and data collection for the prospective study started in October 2022. As of September 6, 2023, 84.6% (186/220) of patients among those in the digital PROM and 15.5% (34/220) of patients among the nonusers have consented to participate. We expect the study to have enough participants by the autumn of 2023. With 1 year of follow-up, the results are expected by spring 2025.

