### Information and Training

The patients will receive information regarding the digital service in consultation, regardless of this research project. If they consent to engage in the digital service, more detailed information on the MyDignio app will be provided by the diabetes specialist nurse. An invitation to download MyDignio will be sent to the patient’s smartphone in consultation, and if they wish and have their national ID with them, they can download MyDignio immediately. The patient interface is easy and intuitive, and extensive training should not be required for most patients.

As the patient interface, the health care personnel site DignioPrevent has been developed to be simple and intuitive. The diabetes specialist nurses have been trained in using the Dignio Connected Care personnel interface DignioPrevent, by personnel from the information and communications technology unit at the university hospital, in addition to a close collaboration with personnel from Dignio Connected Care. Similarly, diabetes health care personnel will receive training in the video consultation systems used in the clinic.

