**Digital user data**						
	**Participation in the digital outpatient care**					
		Yes or no, including start date	✓		✓	

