### Analysis

#### Statistical Analysis

The baseline (T0) and follow-up (T1) variables will be descriptively presented, whereas continuous variables will be analyzed using the median and range if the data are skewed and the mean and SD for normally distributed data. Categorical data will be presented as counts and percentages. The mean change will be estimated by subtracting the baseline scores from the follow-up scores. Any differences in mean changes in short- and long-term variables will be modeled using an ANOVA. To adjust for possible confounders, logistic regression models will include age, gender, and education. We will assess the number of patients tested for eligibility, declined to participate, lost to follow-up, and included in the analysis.

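### T0 is not guaranteed to precede first use of the digital service, so the T1 minus T0 contrast can miss an effect that users have already gained

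*Protocol article*

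**What the plan says.** Results gives the order of events: "The digital solution was implemented in clinical care at the department in November 2021, and the first participant was enrolled in the research project". It dates that first baseline to 27 October 2022. The abstract agrees on the second date: "data collection for the prospective study started in October 2022".

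Under Information and Training, patients hear of the service in consultation "regardless of this research project" and can install the app there. Patient Participants admits people who already use the app as well as those who do not, with no limit on earlier use. Procedures places the baseline questionnaire directly after study consent.

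The primary outcome (Study Outcomes, Overview) is the one-year change in PAM, compared between users and nonusers. Statistical Analysis defines the change: "The mean change will be estimated by subtracting the baseline scores from the follow-up scores". The confounders it names are age, gender and education. Table 3 records participation in the digital service as "Yes or no, including start date", but the stated analysis does not use that date.

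**The concern.** A change score measures the effect of starting a service only if the first measurement comes before the start. Here the service start and the study baseline are set by separate events: a routine consultation and study consent. A patient could have joined the service well before T0.

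For such a patient, T0 PAM already contains whatever the service has achieved, and T1 minus T0 shows only what came later. The same holds for the other outcomes analysed as change, including the EQ-5D-5L difference that feeds the cost-utility analysis. The Aims section promises an evaluation of the effect of participating in digital PROMs, and a mix of new and established users does not estimate that cleanly.

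A second aim is to describe how users differ from nonusers. For prevalent users, patient-reported scores at T0 cannot be read as traits they had before taking up the service.

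**Working it through.** **Inputs.** Service start: November 2021, day not given (Results). First T0: 27 October 2022 (Results). Enrolled by 6 September 2023: "84.5% (n=186) are digital users and 15.5% (n=34) are nonusers in the comparative group", of 220 in total; 186/220 = 84.5% and 34/220 = 15.5%, as stated. Relevant PAM-13 change: 4 points (Sample Size).

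**Gap before the first T0.** The article states no figure for this, so it is calendar subtraction at 30.4375 days per month:
- from 1 November 2021: 360 days, 360/30.4375 = 11.8 months
- from 30 November 2021: 331 days, 331/30.4375 = 10.9 months

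**Attenuation.** Let f be the share of users who started before T0, and g the average share of the effect they had gained by T0. Assume a true effect of 4 points that is complete by T1, is maintained, and is the same for new and prevalent users. New users then show 4 points over T0 to T1, and prevalent users show 4(1 - g). The average is

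(1 - f) x 4 + f x 4(1 - g) = 4 x (1 - f x g).

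| f | g | Visible contrast (points) |
|---|---|---|
| 0.25 | 0.5 | 3.5 |
| 0.5 | 0.5 | 3.0 |
| 0.75 | 0.5 | 2.5 |
| 0.5 | 1 | 2.0 |
| 1 | 0.5 | 2.0 |

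Neither f nor g is in the document, so these rows are a range and not an estimate.

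**What this could mean for power.** The article's 32 per group cannot be reproduced, because it gives no SD, alpha or power. At two-sided 5% and 80% power, 32 per group for 4 points implies an SD of 5.71. On that assumed SD, power with 32 per group falls from 80% to 56% at 3.0 points and to 29% at 2.0 points. The point does not depend on these figures.

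**Precision cost of separating new users.** With a common SD, the standard error is proportional to sqrt(1/n_users + 1/34).

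| Users kept | sqrt(1/n + 1/34) | Increase over 186 |
|---|---|---|
| 186 | 0.1865 | reference |
| 93 | 0.2004 | 7% |
| 62 | 0.2134 | 14% |
| 46 | 0.2262 | 21% |
| 19 | 0.2864 | 54% |

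These are enrolled numbers; dropout is ignored.

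**The case against.** The strongest reply is that the article never says how many of the 186 users started before T0. Sample Size has recruitment continuing until almost everyone at the clinic has been offered the service, and Ethical Considerations links eligibility screening to that offer. Rollout and recruitment probably overlapped, so some users will be new. This stands. A reader might infer that T0 is post-exposure for users in general, and the document does not show that.

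A reader might also take 11 months, or the 21.2 to 22.1 months between service start and 6 September 2023, as users' exposure. Those are ceilings on how long the service was available. Standard care is one consultation a year, with more in some situations, and PROMs are sent with scheduled appointments, although use between visits is possible. Someone who joined months before T0 may have completed few PROMs or none.

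A contrast of 4 x (1 - f) is likewise tempting. It sets g = 1: every prevalent user, even one a month in, has the full effect already.

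One could add that users who gave up before T0 are lost from the user group and bias the result the other way. The document reports nothing on such patients, so this is speculation.

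Finally, the use of the start date in a model may be left to an analysis plan that is not shown, and Limitations promises suitable methods with a statistician. That is fair as to modelling detail. It does not alter what this document fixes: open eligibility, T0 at consent, and a pooled change score. Limitations mentions confounding and bias in general, not exposure before baseline.

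**Conclusion.** The point holds as a gap in the design as written: nothing in the article ensures that T0 comes before first use, and the service had run 10.9 to 11.8 months when the first T0 was taken. For users who started before T0, an effect gained earlier and kept is absent from T1 minus T0, so the contrast understates it. The loss is a fraction f x g of the true effect, and both factors are unknown. It is 1 point of 4 if both are one half, and negligible if few users are prevalent or little had accrued.

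The baseline comparison is affected only where T0 patient-reported scores are read as pre-use traits. Age, sex, education and diabetes duration are not affected, and describing current participants remains valid.

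**What to change.** Use the start date already in Table 3.

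1. Report the distribution of months of use at T0 among users.
2. Before T1 data are analysed, prespecify the users-versus-nonusers PAM change separately for new users and for prevalent users, the latter by months of use at T0.
3. Define new users by a short fixed window around T0 with both a lower and an upper limit. Without an upper limit, a patient who starts late in follow-up would count as a new user with almost no exposure, and the group would be defined by behaviour after baseline.
4. Base any statement about the effect of starting the service on the new-user contrast. If too few users are new, describe the estimate as continued use versus non-use.
5. Present users' T0 scores by new versus prevalent.

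The cost is analysis wording and one derived variable, plus some precision. The loss is modest while a third or more of the 186 users are new, because the 34 nonusers dominate the standard error, but at 19 new users it is large.

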## Discussion

### Overview

We anticipate that this study will generate knowledge on the relevance and effects of participation in digital PROMs for communication and self-management and about the characteristics of users compared with nonusers of the digital PROM. Evaluating the use of digital follow-up might facilitate the need for further development of the tools based on actual clinical use. Finally, investigating the communication between patients and their health care personnel will increase the understanding of how technology impacts consultation.

### Significance of the Study

Although diabetes care has faced considerable improvements in medical equipment facilitation and glycemic control, there is a need for more patient-centered and flexible care using recent developments in digital PROMs in routine care [11,12]. To do so, the possibilities of flexible digital care using PROMs in clinical care must be investigated. The study described in this protocol aims to provide knowledge regarding the characteristics of patients with type 1 diabetes engaged in a digital PROM, their effect on participating in digital PROMs, the patients’ acceptability of consultations prepared and supported by digital and flexible services using PROs, and how these services affect health care personnel.

Although previous research from Norway provides valuable insights into the use of PROMs in clinical diabetes consultations through the DiaPROM study, their findings highlight the need for further investigation into implementation challenges and patient acceptability [57]. In the Danish DiabetesFlex study, PROMs in the diabetes outpatient clinic had a positive impact on patients’ management of their diabetes and their responsibility for care plans. Compared with standard care, using PROM in flexible visits improved diabetes-related well-being and decreased face-to-face visits while maintaining safe diabetes management [16,24]. Using a PROM, patients were encouraged to reflect on their diabetes management; this led to a more tailored and individualized treatment approach and made the consultations more flexible, allowing for a broader dialogue between patients and health care providers [24]. Similarly, diabetes care support is crucial when living with diabetes [58]. Using PROMs in diabetes specialist care can improve communication, enhance patient engagement in their care, and improve patient outcomes. Nonetheless, it remains necessary to explore the acceptability of the use of digital PROMs to prevent inequality in health for patients who do not engage in digital health care and, as such, do not receive the intended care [18], while also identifying the barriers preventing these patients from accessing care and exploring alternative ways of delivering health care services and support. This study will investigate the effects and acceptability of a digital PROM, emphasize the potential benefits and barriers by further exploring the impact of using a PROM in a diabetes outpatient clinic, and, as such, add knowledge to existing evidence.

### Limitations

In evaluating the implementation of digital tools and PROMs, a randomized controlled trial could be considered the gold standard to minimize confounding variables and provide stronger evidence. In this case, to design a control group, we would have to withhold the tools from patients in the clinic, which could be considered unfair clinical practice in the clinic. We could have chosen to have a control group at another hospital. However, practices in endocrinology outpatient clinics are changing, making it difficult to find a hospital department administering the usual care. Therefore, this study has been planned as an observational quasi-experimental design, with its limitations being potential confounding variables and bias. This is a novel study, and we plan to include numerous participants with a long follow-up period. We will minimize bias and confounding by including patients engaged in digital PROMs and patients choosing traditional care, controlling for known confounders, and using appropriate statistical methods to analyze data in collaboration with a statistician.

A potential limitation, according to the qualitative part of the study, is related to the conduct of the observations of consultations with patients and being interviewed about their practice, with a potential risk for reactivity of social desirability bias. Diabetes health care personnel might modify their behavior while being observed to conform to expectations about performance. Similarly, they could provide responses in the interviews that they believe are socially acceptable, rather than giving honest and accurate answers. It will be important for the researchers to establish trust and ensure that the responses are kept confidential and not used to evaluate performance.

### Conclusions

There is a need for elaborate knowledge on patient participation in digital tools using PROMs in diabetes specialist care. A multimethod prospective observational cohort study can provide valuable insights into the effectiveness and acceptability of PROM digital tools, aiming for a broad measurement of their full-scale implementation in a large diabetes outpatient clinic.

## Appendix

Multimedia Appendix 1 Screenshot of the MyDignio interface.

Multimedia Appendix 2 Screenshot of the DignioPrevent interface.

Multimedia Appendix 3 Interview guide—patients.

Multimedia Appendix 4 Interview guide—health care professionals.

## Abbreviations

HbA_1c_: glycated hemoglobin
HLS19-DHC-NO: Health Literacy Survey-19 Digital Health Care in Norwegian
PAM: Patient Activation Measure
PRO: patient-reported outcome
PROM: patient-reported outcome measure
SPIRIT: Standard Protocol Items: Recommendations for Interventional Trials
